## **15. Evaluation criteria for effectiveness, and evaluation and interpretation methods (statistical analysis)**

### **15.1. Primary Endpoint**

In-hospital death

### **15.2. Secondary Endpoints**

- 1) Death in 28 days
- 2) Death during follow-up
- 3) Death, myocardial infarction, stroke, re-admission due to heart failure during follow-up
- 4) Number of days of intensive care unit
- 5) Hospitalization days
- 6) Lactate 24 hour clearance
- 7) Successful removal of left ventricular assist device (IABP, ECMO)

### **15.3. Statistical analysis**

We aim to identify predictors of in-hospital death in patients who experience shock using binary logistic regression analysis. This type of analysis requires 10-15 events per independent variable, and with an expected mortality rate of about 40%, or approximately 400 deaths, we have sufficient events to study various risk factors. The goodness-of-fit of the model will be assessed using the C-statistic and Hosmer-Lemeshow test. In addition, we plan to compare the in-hospital death rate between patients with and without left ventricular assist devices using chi-square tests among those who receive a certain level of vasoactive drugs. We also aim to identify predictors of successful removal of the ECMO device and procedure-related complications such as bleeding, thrombosis, and limb ischemia using binary logistic regression analysis in patients who undergo ECMO. Finally, we plan to evaluate overall death over five years using Cox survival

analysis. We will assess the goodness-of-fit of the model by checking Schoenfeld's residuals and identify the hazard of each risk factor.

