## 9.3. Targeted sample size and their basis

- (1) Estimated enrollment: 1000 participants (competitive registration after registering 1,000 participants)

- The group with left ventricular assist device insertion: more than 400 participants
- The group without left ventricular assist device insertion: more than 600 participants

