### (2) Background

Samsung Medical Center, Korea University Anam Hospital, Sejong General Hospital, Bucheon, Samsung Changwon Hospital, Ilsan Paik Hospital, Dankook University Medical Center, Konkuk University Medical Center, Chung-Ang University Hospital, Inha University Hospital, and Chungbuk National University Hospital are expected to participate, and considering the fact that 1,800 patients with acute myocardial infarction are being treated annually in 10 hospitals, about 5.5% of myocardial infarction patients progress to shock, which means that about 100 patients can be registered each year, and it is estimated that more than 100 patients can be registered due to other causes such as unstable angina, shock during procedures, cardiomyopathy, and myocarditis. Considering the five-year study period, it is estimated that more than 1,000 patients can be registered.

As for the group with left ventricular assist devices (LVADs) inserted, most of them are critically ill patients, so it should be noted that a comparison with the group without LVADs inserted cannot be made on an equal footing. However, other than that, sample size/power calculations for binomial proportions were applied using Fleiss, Tytun, and Ury (1980). With the above number of patients, it has about 88% statistical power to detect an odds ratio of 1.56 (inserted group = 0.3, non-inserted group = 0.4). However, if an expected dropout rate of about 10% is taken into account, the power is reduced to 84%.

In addition, considering that the group with LVADs inserted is significantly superior to the group without LVADs, a one-sided test is usually performed, and when adjusted, the power exceeds 90%. Therefore, it is expected that this clinical trial plan will be statistically and clinically successful when executed.

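### Section 15.3 treats the C-statistic as goodness of fit and names no overfitting correction; at its own rule's predictor ceiling, an uncorrected C-statistic is about 0.02 to 0.06 too high

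*Protocol*

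**What the plan says.** Section 15.3 gives the aim of the main model: "We aim to identify predictors of in-hospital death in patients who experience shock using binary logistic regression analysis". It then argues that the registry is large enough. The rule is "This type of analysis requires 10-15 events per independent variable", and the conclusion is that "with an expected mortality rate of about 40%, or approximately 400 deaths, we have sufficient events to study various risk factors". The next sentence fixes how the model is judged: "The goodness-of-fit of the model will be assessed using the C-statistic and Hosmer-Lemeshow test".

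The section does not say how many predictors will be fitted, how they will be chosen, or on which data the two measures will be computed. It names no bootstrap, cross-validation or validation sample. Logistic models for ECMO removal and for procedure-related complications come later in the same section, with no performance measure stated for them.

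The size of the registry is in section 9.3: "Estimated enrollment: 1000 participants (competitive registration after registering 1,000 participants", with minimum group sizes of 400 with a device and 600 without.

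**The concern.** There are two difficulties with the stated method.

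First, the label is wrong. The C-statistic says how well the model ranks patients who die above those who survive. A model can rank well and still give probabilities that are badly off, so a high C-statistic is not evidence of fit.

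Second, neither named measure shows overfitting when computed on the fitting data. The C-statistic is then biased upward, because the coefficients were tuned to those same patients. The Hosmer-Lemeshow test does address calibration. However, a maximum-likelihood logistic model has a calibration slope of exactly 1 on its own data, so the test has little to find there. Its p-value also depends on grouping and sample size, and it does not give the size of any miscalibration.

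Finding prognostic factors is one of the study's stated purposes. At stake is whether the reported performance of the resulting model would carry over to new patients.

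**Working it through.** **Inputs from the Protocol**
- Enrolment 1,000, with groups of at least 400 and 600 (section 9.3).
- Expected mortality about 40%, and 10-15 events per variable (section 15.3).
- Planning rates of 0.3 with a device and 0.4 without (section 9.3, Background: "it has about 88% statistical power to detect an odds ratio of 1.56 (inserted group = 0.3, non-inserted group = 0.4"). That text does not name the outcome; I read it as in-hospital death.

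**The plan's own figures**
- Deaths: 0.40 × 1,000 = 400, as stated.
- Odds ratio: (0.4/0.6) / (0.3/0.7) = 1.556, as stated. With continuity correction and a two-sided 5% level (assumed), power at 400/600 is 88.9%, against about 88% stated. The planning rates are therefore read correctly.
- Deaths from those rates: 0.3 × 400 + 0.4 × 600 = 120 + 240 = 360.

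**Predictor ceiling = deaths / events per variable**
- 400 deaths: 400/15 = 26.7, so 26; 400/10 = 40.
- 360 deaths: 360/15 = 24; 360/10 = 36.

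The rule therefore allows at most 24 to 40 predictors.

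**Optimism = C-statistic on the fitting data minus C-statistic in new patients**

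Assumptions: independent normal predictors of equal effect, maximum-likelihood fit, no variable selection, 40% event rate, 100 simulated data sets per setting, and 10,000 new patients for testing. The 360-death rows use 900 patients (0.40 × 900 = 360). Monte Carlo error on C is about 0.005.

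| Deaths | Predictors | True C 0.70 | 0.75 | 0.80 | 0.85 |
|---|---|---|---|---|---|
| 400 | 10 | 0.015 | 0.008 | 0.003 | 0.007 |
| 400 | 26 | 0.042 | 0.036 | 0.023 | 0.019 |
| 400 | 40 | 0.059 | 0.045 | 0.036 | 0.027 |
| 360 | 24 | 0.035 | 0.027 | 0.024 | 0.020 |
| 360 | 36 | 0.053 | 0.047 | 0.044 | 0.034 |

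For example, with 40 predictors and a true C of 0.75, the fitting-data value is 0.771 and the new-patient value 0.726, a difference of 0.045. Across the four ceiling rows the range is 0.019 to 0.059.

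**Does Hosmer-Lemeshow show it?** In the same ceiling rows the calibration slope in new patients is 0.695 to 0.905, where 1 means no overfitting. The test on the fitting data (10 groups, 8 degrees of freedom) rejects at 5% in only 1% to 9% of runs, roughly its nominal rate.

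**Effect of selection.** When 30-40 candidates were screened by univariable p < 0.05 or p < 0.20, about 9-15 predictors remained. Optimism was 0.016 to 0.035, more than the 0.003 to 0.015 for 10 predictors fixed in advance.

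**Does bootstrap correction work?** This was a smaller run: true C 0.75, 15 data sets, 40 resamples each.

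| Predictors | Fitting data | Corrected | New patients |
|---|---|---|---|
| 26 | 0.762 | 0.735 | 0.733 |
| 40 | 0.773 | 0.733 | 0.727 |

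The error falls from 0.029 to 0.002 with 26 predictors, and from 0.046 to 0.006 with 40.

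**The case against.** The strongest reply is that section 15.3 never says the C-statistic will be uncorrected or computed on the fitting data. It is silent, and internal validation is commonly left to the SAP, which is not shown. That stands: the absence of a validation plan is not held against the protocol here. What remains is a stated method with a wrong label, and two named measures that do not reveal overfitting unless something is added to them.

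A second reply is that 24 to 40 is a ceiling, not a plan, and that with 10 predictors the optimism is small. That also stands. A large candidate pool is plausible, though. Section 12.1 lists 16 laboratory variables. Age, sex, height, weight, blood pressure and heart rate bring the count to 22, before risk factors, diagnosis, medication, echocardiography and angiography. Reducing such a pool by looking at the data brings part of the optimism back.

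Some stronger inferences are not supported:
- **That Hosmer-Lemeshow overstates discrimination.** It is a calibration test and cannot. Its weakness is insensitivity to overfitting.
- **That the ECMO models are known to be badly optimistic.** The goodness-of-fit sentence refers to the death model and precedes the ECMO models. The documents give no ECMO patient number, complication rate or predictor count, so any figure would rest on invented inputs.
- **That a main conclusion is biased.** The stated aim is to identify predictors, and no risk score is announced.

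**Conclusion.** The point holds as a cheap improvement. Section 15.3 mislabels the C-statistic as goodness of fit and names no correction for overfitting. If the C-statistic is computed on the fitting data, it is too high by about 0.02 to 0.06 at the 24 to 40 predictors the plan's rule permits, and by about 0.01 with 10 predictors fixed in advance. Data-driven selection would add to this. The Hosmer-Lemeshow test on the same data would usually not reveal it.

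These sizes rest on assumptions the Protocol does not settle: computation on the fitting data, a true C-statistic of 0.70 to 0.85, and independent predictors of equal effect. Weaker discrimination would give more optimism: at a true C of 0.60 it is 0.062 with 26 predictors and 0.086 with 40.

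A reader might infer that the comparison of in-hospital death between patients with and without a device is affected. It is not: that comparison is a separate chi-square test. Only the reported performance of the prognostic model is touched.

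**What to change.** In section 15.3:
- Describe the C-statistic as a measure of discrimination, and report it with bootstrap optimism correction, repeating any variable selection in each resample.
- Report an optimism-corrected calibration slope and a smoothed calibration plot, in place of reliance on the Hosmer-Lemeshow p-value.
- Apply the same to the ECMO models if their performance is reported.

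No new data are needed. The cost is a little more analysis code and a slightly less favourable reported C-statistic.

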| Duration                       | IRB approval date ~ December 31, 2019 (registration period: IRB approval date ~ December 31, 2018).
Data collection period: January 1, 2014 ~ December 31, 2019 (6 years).                                                                                                                                                                                                                                                                                                                                                                                                                                                                                                                                                                                                                                                                                                                                                                                                                                                                                                                                                       |
| Design                         | Retrospective and prospective, open, multi-center, and observational registry study                                                                                                                                                                                                                                                                                                                                                                                                                                                                                                                                                                                                                                                                                                                                                                                                                                                                                                                                                                                                                                                 |

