**6. Purpose and background of clinical trial****6.1. Purpose**

The purpose of this study is to investigate the treatment status and clinical outcomes of cardiogenic shock in Koreans, as well as identify factors that can improve prognosis through retrospective and prospective registration of patients with cardiogenic shock from multiple institutions in Korea. In addition, we aim to determine the current usage and treatment effects of IABP and ECMO for cardiogenic shock.

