### **11.2. Insertion of left ventricular assist devices**

The insertion of a left ventricular assist device is typically performed according to the recommendations of the American Heart Association and the Korean Society of Cardiology when drugs are not effective. However, in exceptional cases such as myocardial infarction with left ventricular wall motion abnormalities that are expected to result in cardiac arrest, the decision to insert IABP and ECMO more aggressively is left to the discretion of the operator. After the insertion of a left ventricular assist device, anticoagulant therapy should be administered to prevent thromboembolism unless it is contraindicated, and in order to prevent limb ischemia, the insertion of a catheter for limb perfusion is recommended if there is no palpable doppler signal or a change in limb color is detected. If pulmonary edema and pulmonary hemorrhage occur due to left ventricular dilatation after ECMO insertion, percutaneous or surgical decompression is recommended.

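### The only stated device comparison is a pooled chi-square test between groups the protocol calls unequal, so it will mix severity with any effect of IABP or ECMO

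*Protocol*

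**What the plan says.** Protocol 6.1, repeated in the Summary, sets a treatment-effect aim beside the descriptive one: "we aim to determine the current usage and treatment effects of IABP and ECMO for cardiogenic shock". The Summary gives the design as "Retrospective and prospective, open, multi-center, and observational registry study", so devices are not allocated at random.

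Section 9.3 (2) says of device patients that "most of them are critically ill patients" and that "a comparison with the group without LVADs inserted cannot be made on an equal footing". Section 11.2 explains why. Insertion typically follows the recommendations of the American Heart Association and the "Korean Society of Cardiology when drugs are not effective", while in exceptional cases "the decision to insert IABP and ECMO more aggressively is left to the discretion of the operator".

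Section 15.3 then plans to "compare the in-hospital death rate between patients with and without left ventricular assist devices using chi-square tests", limited to patients "among those who receive a certain level of vasoactive drugs". The level is not defined. No covariate, matching, weighting, stratification or centre term is attached to this comparison. The logistic models in the same section are for predictors of in-hospital death and, in ECMO patients, of device removal and complications. The Cox model is for overall death and the hazard of each risk factor. None is said to estimate an adjusted device effect.

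**The concern.** A device given mainly when drugs have failed goes to patients whose risk of death is already higher. A comparison of crude proportions charges that extra risk to the device. It can hide a real benefit or show harm where there is none, and a larger sample only makes the wrong answer more precise.

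The restriction to patients on vasoactive drugs may narrow the imbalance. But age, cause of shock, cardiac arrest and lactate can still differ within any drug level. Section 11.1 also records the maximum dose used for shock treatment, without saying that it precedes insertion. If that maximum defines the subset, the subset may depend on what happened after the device went in.

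Pooling is a second gap. Section 6.2 reports a randomised trial that did not show IABP to be superior and then describes large expected benefits of ECMO. One device-versus-none contrast cannot give either effect separately.

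The matter is not marginal, because the power statement in 9.3 rests on this comparison and in-hospital death is the primary endpoint.

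**Working it through.** **Step 1: the plan's own power.** Inputs from 9.3: n₁ = 400 with a device, n₂ = 600 without, death rates 0.3 and 0.4. Alpha is not stated; 0.05 is assumed.

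- Odds ratio: (0.4/0.6)/(0.3/0.7) = 1.556, against the stated 1.56.
- Fleiss–Tytun–Ury correction with r = 1.5 and d = 0.1: m = 400 − (r+1)/(r·d) = 400 − 16.7 = 383.3.
- Pooled rate p̄ = (0.3 + 1.5 × 0.4)/2.5 = 0.36.
- Power = Φ{[d√(m·r) − 1.96√((r+1)p̄(1−p̄))]/√(r·p₁(1−p₁) + p₂(1−p₂))} = Φ{(2.398 − 1.487)/0.745} = Φ(1.22) = 0.889, against the stated 88%.
- At 360/540, after 10% dropout: 0.853, against 84%. One-sided: 0.939 and 0.915, against more than 90%.

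The arithmetic holds. It describes the effect of a device only if the two groups would otherwise have the same risk of death, which the same section denies.

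**Step 2: what a severity imbalance does.** None of the inputs below is in the documents except the 40% mortality without a device, the 400/600 split and the target odds ratio (1/1.556 = 0.643). Assume one binary severity marker, present in a share q_D of device patients and q_N of the others, with odds ratio k for death.

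- Find p₀ (mortality without the marker) and p₁ (with it) such that p₁/(1−p₁) = k·p₀/(1−p₀) and q_N·p₁ + (1−q_N)·p₀ = 0.40.
- For a true device odds ratio θ, put f(p) = θp/(1 − p + θp). Device mortality is P = q_D·f(p₁) + (1−q_D)·f(p₀).
- Crude odds ratio = [P/(1−P)]/(0.4/0.6). The rejection rate uses the Step 1 formula with P and 0.40.

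First row worked through, with no device effect: p₀ = 0.333 and p₁ = 0.500, since 0.4 × 0.500 + 0.6 × 0.333 = 0.40. Then P = 0.5 × 0.500 + 0.5 × 0.333 = 0.417, and the crude odds ratio is (0.417/0.583)/0.667 = 1.07.

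| Marker, device vs none | k | p₀, p₁ | P, no effect | Crude OR | Test declares harm | P, true OR 0.643 | Crude OR | Power to show benefit |
|---|---|---|---|---|---|---|---|---|
| 50% vs 40% | 2 | 0.333, 0.500 | 41.7% | 1.07 | 7% | 31.7% | 0.70 | 74% |
| 60% vs 30% | 2 | 0.350, 0.518 | 45.1% | 1.23 | 33% | 34.8% | 0.80 | 36% |
| 60% vs 30% | 3 | 0.320, 0.586 | 48.0% | 1.38 | 68% | 37.9% | 0.91 | 9% |

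The harm column counts rejections in that direction only, where the nominal rate of a two-sided 5% test is 2.5%.

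**Step 3: allowing for the restriction.** The chi-square is planned in a subset of unstated size. In the last row, if 80% of each group qualifies (320/480), harm is declared in 58% of studies; if 50% qualifies (200/300), in 39%. These figures keep the imbalance at 60% versus 30%. A sensible restriction should also narrow it, so they may still be too high.

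**The case against.** The protocol does not ignore severity. It warns the reader in 9.3, and it limits the comparison by vasoactive treatment, which bears directly on the indication in 11.2. A reader might infer that severity is left wholly uncontrolled. That goes too far: restriction is a form of control. What remains is that the level is undefined, its timing relative to insertion is not given, and other aspects of severity vary within it.

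A reader might also infer that the result will show severity instead of the device effect, or that a false finding of harm in about two studies of three is to be expected. The documents support neither. They give no severity distribution, so the 68% is one strong assumed case at full sample size. In the mildest row the test declares harm in 7% of studies and most of a true benefit stays visible.

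Third, a reader might treat centre as an established confounder. The protocol does not say that device use or mortality differs between hospitals. It is a plausible inference from operator discretion across ten expected sites, and no more.

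Finally, the device comparison is introduced as an addition to the prognostic models, which are unaffected, and a statistical analysis plan may hold the details of an adjusted analysis. That is fair for a covariate list or a weighting scheme. It does not cover a protocol that names the chi-square as its method for this comparison and bases its power on it.

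**Conclusion.** The point stands. The protocol asks for treatment effects, concedes that the groups are unequal, and fixes a test that corrects for this only through an undefined restriction. Followed as written, it gives an answer that mixes severity with any device effect, and it gives no separate answer for IABP and ECMO.

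The direction of the bias, against the device, follows from the protocol's own description of who receives one. Its size cannot be derived from the documents. The range shown rests on a single assumed binary marker, 40% mortality without a device, an alpha of 0.05 and the planned 400/600. The stated 88% power is computed correctly but does not carry over to a comparison confounded by severity.

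**What to change.** In 15.3:

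- Keep the chi-square as a descriptive comparison.
- Make the main device comparison a pre-specified adjusted analysis, by multivariable logistic regression or propensity-score weighting. Use severity covariates the study already collects: age, cause of shock, in-hospital arrest, blood pressure, lactate, creatinine and vasoactive dose.
- Take these values from before insertion. The worst vital signs of the day and the maximum doses in 11.1 should not be used where they may follow insertion. The flow chart's six-hourly lactate from shock onset helps here.
- Include centre as a plausible further confounder.
- Define the vasoactive level for this analysis, from pre-insertion data.
- Report IABP versus none and ECMO versus none separately, with odds ratios and 95% confidence intervals, and state that unmeasured severity may remain.

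The cost is protocol wording, analysis time and some care in establishing what preceded insertion; no new patients or procedures are needed. The expected deaths, about 400 in 15.3, would carry 400/15 = 26 to 400/10 = 40 terms by the protocol's own rule, so the model is affordable.

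Precision falls. If the covariates explain 10% to 40% of device use (assumed; effective sample n × (1 − R²), no continuity correction), power at 0.3 versus 0.4 drops from 90% to between 87% and 71% with 1,000 patients. Device-specific estimates will be less precise than a pooled one.

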## 6.2. Background

Cardiogenic shock usually occurs as a fatal complication of acute myocardial infarction, cardiomyopathy, myocarditis, and rarely, sepsis. In particular, shock occurs in 5-8% of cases of ST-segment elevation myocardial infarction, and despite the development of various treatment techniques such as coronary intervention and coronary artery bypass grafting, a very high mortality rate of about 40% is still reported [1]. Shock is a term that encompasses all clinical situations in which cellular respiration is not properly carried out due to inadequate oxygen supply to tissues. It was first described by a French surgeon in 1737, and much progress has been made in the treatment and research of shock through the two World Wars and the Korean and Vietnam Wars. Types of shock include hypovolemic shock, represented by excessive bleeding due to trauma or surgery, septic shock caused by decreased peripheral vascular resistance due to infection, obstructive shock caused by circulatory disorders such as pulmonary embolism and cardiac tamponade, and cardiogenic shock caused by decreased cardiac output due to loss of cardiac pump function. The prominent characteristic of cardiogenic shock is that while the early mortality rate is the highest, once the patient recovers from shock, they can maintain a good quality of life with a better prognosis compared to other shocks. Currently, most of the studies related to cardiogenic shock published in Korea have selected patients through the arbitrary criterion of Killip class IV in acute myocardial infarction registry, so it is difficult to accurately determine the frequency and treatment status, mortality rate, etc. of cardiogenic shock caused by causes other than myocardial infarction. Since the adequacy of appropriate early treatment within 24 hours after the occurrence of cardiogenic shock determines the prognosis, it is essential to evaluate the treatment status and appropriateness of cardiogenic shock in Korea through research at the present time. In addition, the initial treatment of cardiogenic shock is primarily fluid therapy, mechanical ventilation, and vasopressor therapy, but if these are ineffective, left ventricular assist devices such as intra-aortic balloon pumps (IABP) and extracorporeal membrane oxygenation (ECMO) can be used. However, there are still no large-scale systematic studies in Korea to determine their effects.

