Recently, in a study conducted by Thiele et al., the superiority of IABP treatment was not demonstrated compared to standard treatment group in patients with cardiogenic shock accompanied by acute myocardial infarction for whom early coronary intervention was scheduled [2]. As a result, research on the effectiveness and safety of mechanical circulatory support devices that can more effectively assist left ventricular function in cardiogenic shock is being actively pursued worldwide [3-6]. In particular, the expected benefits of ECMO, a left ventricular assist device that can be operated anywhere in emergency situations, are significant, and interest in ECMO procedures is rapidly increasing in Korea, with the number of procedures increasing rapidly. Therefore, it is urgent to evaluate the appropriateness and effectiveness of ECMO and conduct research on its effects.

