## **9. Inclusion criteria, exclusion criteria, and targeted sample size and their basis**

### **9.1. Inclusion criteria**

1. 19 years old or older
- 2-1). Systolic blood pressure is less than 90mmHg for more than 30 minutes despite the fluid therapy, or Use of pressure boosting agents is necessary.
- 2-2). Peripheral hypoxia (cold skin, urine less than 30 cc per hour, impaired consciousness, lactate  $\geq 2.0$  mmol / l) or a person with pulmonary edema.
3. Causes of cardiogenic shock include acute myocardial infarction (including in coronary intervention), cardiomyopathy, myocarditis, pulmonary embolism, refractory ventricular tachycardia, shock during coronary intervention.
4. In-hospital cardiac arrest as a result of the cause stated in 'inclusion criteria 3'.
5. Those voluntarily consenting to the medical records and the data necessary for the study during the entire study period.

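### Section 15.3 fixes the device comparison of in-hospital death as one chi-square pooled over all causes of shock, so the result can be confounded by cause or average over different effects

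*Protocol*

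**What the plan says.** **Analysis (Protocol 15.3).** The plan is to "compare the in-hospital death rate between patients with and without left ventricular assist devices using chi-square tests". The only restriction is to patients who received some unspecified level of vasoactive drugs. Cause of shock appears neither as a stratum nor as an adjustment. A separate logistic model looks for predictors of in-hospital death in all shock patients, with no covariate list.

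**Population (9.1 and 9.3).** Besides acute myocardial infarction, the eligible causes are "cardiomyopathy, myocarditis, pulmonary embolism, refractory ventricular tachycardia, shock during coronary intervention". On intake, 9.3 says "about 5.5% of myocardial infarction patients progress to shock, which means that about 100 patients can be registered each year", and that "more than 100 patients can be registered due to other causes such as unstable angina, shock during procedures, cardiomyopathy, and myocarditis".

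**Rationale (6.2).** Existing Korean studies draw on infarction registries, so "it is difficult to accurately determine the frequency and treatment status, mortality rate, etc. of cardiogenic shock caused by causes other than myocardial infarction". A further gap concerns IABP and ECMO: "there are still no large-scale systematic studies in Korea to determine their effects". The IABP trial described there was "in patients with cardiogenic shock accompanied by acute myocardial infarction for whom early coronary intervention was scheduled".

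**Data.** Cause is part of eligibility (9.1, criterion 3), and clinical diagnosis is recorded at Visit 1 (12.1).

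**The concern.** By the protocol's own intake figures the registry is about half infarct and half other shock. The second half is itself mixed. It includes pulmonary embolism, which 6.2 describes as a cause of obstructive shock rather than pump failure.

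Two things can go wrong when one two-by-two table is formed over such a population:

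- **Confounding by cause.** If operators use devices more often in one cause, and that cause has a different death rate, the crude comparison shows a difference that has nothing to do with the device.
- **Averaging.** If the device effect differs by cause, the single figure describes neither half. It may suggest a benefit for all when only one half benefits, or none when the effects cancel.

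A plain chi-square cannot deal with either. The reader would be left with a device result that may partly reflect case mix, in a registry set up in part because non-infarct shock is poorly described.

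**Working it through.** **Inputs from the protocol.** 1,800 infarctions a year, 5.5% progressing to shock, more than 100 other-cause patients a year, five years; 400 device and 600 non-device patients; 30% versus 40% in-hospital death; power about 88%; about 400 deaths in all. Two-sided alpha of 0.05 is assumed, because the protocol does not state it.

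**1. Intake by cause.** 1,800 × 0.055 = 99 a year, or 495 in five years, against at least 500 others. I use 500 and 500.

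**2. The plan's own power, pooled.** With p̄ = (400 × 0.30 + 600 × 0.40)/1,000 = 0.36:

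power = Φ{[0.10 − 1.96·√(0.36 × 0.64 × (1/400 + 1/600))] / √(0.21/400 + 0.24/600)} = Φ{(0.10 − 0.0607)/0.0304} = Φ(1.29) = 90.2%.

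The continuity correction of the cited method replaces 400 by 400 × [1 − (1 + 1/1.5)/(2 × 400 × 0.10)]² = 383.5, which gives 88.9%. The stated 88% is reproduced to within a point, for the pooled comparison only.

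**3. Confounding by cause, with no device effect (assumed rates).** Let mortality be 50% in infarct and 30% in other shock. Deaths are 250 + 150 = 400, matching the planned total. Let x of the 400 device patients be non-infarct. Then device mortality = 0.50 − 0.20·x/400, and non-device mortality = 0.50 − 0.20·(500 − x)/600. The standard error is √(0.24 × (1/400 + 1/600)) = 3.16 points.

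| x | Device | No device | Difference (points) | z |
|---|---|---|---|---|
| 100 | 45.0% | 36.7% | +8.3 | 2.6 |
| 150 | 42.5% | 38.3% | +4.2 | 1.3 |
| 200 | 40.0% | 40.0% | 0 | 0 |
| 250 | 37.5% | 41.7% | −4.2 | −1.3 |
| 300 | 35.0% | 43.3% | −8.3 | −2.6 |

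The bias is the mortality gap times the difference in non-infarct share between the groups. At x = 300 that is 0.20 × (75% − 33.3%) = 8.3 points. A gap of 10 points instead of 20 halves every difference in the table.

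**4. The same data, stratified (x = 300).** Infarct: 50/100 versus 200/400 deaths. Other: 90/300 versus 60/200. The Mantel-Haenszel odds ratio is (50 × 200/500 + 90 × 140/500)/(50 × 200/500 + 210 × 60/500) = (20 + 25.2)/(20 + 25.2) = 1.00. The crude odds ratio is (0.35/0.65)/(0.433/0.567) = 0.70.

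**5. Averaging (assumed rates; 200 device and 300 non-device in each half).**

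- 40% v 40% in infarct and 20% v 40% in other shock: pooled device rate (80 + 40)/400 = 30% against 40%, the same as the planning effect.
- 30% v 40% and 50% v 40%: pooled device rate (60 + 100)/400 = 40% against 40%, so both effects vanish.

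**6. Price of stratifying.** At 200 v 300 within a half, power for 30% v 40% is 59% with the continuity correction and 63% without. Other splits of 500, with correction: 250/250 61%, 150/350 53%, 100/400 40%. The 95% half-width of the difference is 1.96·√(0.21/200 + 0.24/300) = 8.4 points, against 6.0 for the whole registry. An interaction test has about 89% power when the effects are −10 and +10 points, but only about 36% when they are −10 and 0.

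**The case against.** The strongest reply is that strata, covariates and subgroup tables are usual content of a statistical analysis plan, which is not shown. That stands for the logistic model. Section 15.3 lists no covariates and speaks of various risk factors, and diagnosis is recorded, so cause may well be included. It does not stand for the device comparison, where 15.3 itself names the test and its population.

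Several further points are fair:

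- The non-infarct gap in 6.2 is descriptive and one of several. The device gap and the purpose in 6.1 name no cause. An average effect across cardiogenic shock is therefore a legitimate target, provided it is not distorted by case mix.
- A reader might infer that half the registry gets no answer of its own. The protocol does not support that: tables by diagnosis can be produced from data already collected, and nothing in 15.3 rules them out.
- A reader might also infer that opposite device effects are being hidden. No figure in the protocol suggests opposite, or even different, effects. The rates in steps 3 and 5 are chosen to show what the test cannot detect.
- Other causes in 9.3 include unstable angina and procedural shock, so that group is not cleanly non-infarct.
- Section 9.3 already concedes that device patients are sicker. That is probably the larger threat, and stratifying by cause does not remove it.

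**Conclusion.** The point holds for the device comparison. Section 15.3 fixes a method that ignores a recorded variable likely to matter, in a registry planned to be about half infarct and half other shock.

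The possible size is material. Under the assumed 50% and 30% mortality, the spurious difference runs from 0 to 8.3 points in either direction as the non-infarct share of device patients moves from 50% to 75% or 25%. The planning effect is 10 points. With smaller gaps in mortality or device use it shrinks in proportion, and with equal device use by cause it is zero. The protocol gives neither mortality nor device use by cause: its figure of about 40% comes from infarction in 6.2 and is applied to the whole registry in 15.3. The conclusion is therefore that the planned test is open to this error, not that the error will occur.

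**What to change.** In 15.3:

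- Replace the plain chi-square with a comparison stratified by recorded cause, infarct versus non-infarct, using a Mantel-Haenszel estimate or a logistic model with a cause term.
- State in advance how procedural shock and unstable angina are assigned.
- Report in-hospital death and the device estimate in each stratum with 95% intervals.
- Give the device-by-cause interaction as an estimate with its interval. With about 36% power for a 10-point contrast, a non-significant test would say little.
- Name cause as a covariate in the mortality model. I would not add interactions of cause with an open list of predictors, which brings multiplicity without a hypothesis.

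The cost is wording only, because cause and diagnosis are already collected. The price is precision: about 59 to 63% power within a half at an assumed 200 v 300, and lower once the vasoactive restriction reduces the numbers. Confounding by severity needs its own adjustment, and the text should say that stratifying by cause does not provide it.
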